**Aim 1: Efficacy of SCOPE-PP (*****Primary Outcomes)***			
Efficacy of SCOPE-PP	**Perfect Persistence:** Persistence on PrEP (%, time on PrEP adherent). Perfect persistence in postpartum = > 950 fmol/punch in DBS TFV-DP), by study arm	DBS TDF-DP	RCT 1: 6 months RCT 2: 15 months postpartum
	**Prevention-Effective Persistence:** Persistence on PrEP when sexually active (in postpartum women = > 950 fmol/punch in DBS TFV-DP), by study arm	DBS TDF-DP	RCT 1: 6 months RCT 2: 15 months postpartum
	**Self-reported persistence:** self-reported measures of PrEP use and pill counts over the phone	Self-reported PrEP persistence &pill count	Quarterly
	**Secondary outcomes**: HIV incidence (maternal and infant), adverse events and IPV	RedCap clinical data	Monthly
**Nested implementation science evaluation of SCOPE-PP acceptability, feasibility using CFIR**			
Ickovic’ and Meisler’s Conceptual Factors	Evaluate factors associated with PrEP persistence in conceptual model: individual level (including partner PrEP support), facility level, HIV level (partner HIV testing & serostatus)	Quantitative surveys at each visit	Baseline, 1 month, 6 months, 12 months postpartum
Acceptability and uptake of intervention	Organizational, providers, woman and partner views on acceptability of SCOPE-PP including HIVST, urine TFV testing for persistence monitoring, and differentiated care	Mixed methods	At 6 months & 12 months follow-up of all participants (survey); IDIs in 20 providers working with PrEP, 30 participants & 30 partners
Feasibility of intervention	Organizational, providers, woman and partner views on feasibility & scalability of implementation of SCOPE-PP	Mixed methods surveys	
**Aim 2: Evaluate cost effectiveness of SCOPE-PP**			
Incremental cost of Scope-PP	Based on micro-costing, evaluate incremental cost per participant of SCOPE-PP from baseline to 6, 12 and 15 months postpartum by trial step	Quantitative surveys at each visit	RCT 1: 6 months RCT 2: 15 months postpartum
Incremental cost per improved PrEP continuation and persistence	Using trial-based cost-effectiveness analysis, evaluate incremental cost per improved PrEP continuation and persistence at 6, 12 and 15 months postpartum for SCOPE-PP (integrating step 1 and step 2 trials)	Quantitative surveys at each visit	RCT 1: 6 months RCT 2: 15 months postpartum
Incremental cost per DALY averted	Using model-based cost-utility analysis, evaluate incremental lifetime cost and DALYs averted for SCOPE-PP and assess value for money	N/A	N/A (model-based analysis)

*SCOPE-PP* Stepped care to optimize pre-exposure prophylaxis (PrEP) effectiveness in pregnant and postpartum women, *DALY* disability adjusted life year, *CFIR* Consolidated Framework for Implementation Research, *PrEP* pre-exposure prophylaxis, *HIVST* HIV self-testing, *TFV-DP* tenofovir diphosphate

### Nested implementation science data

SCOPE-PP outcomes, measures, data sources, and timing are summarized in Table 4. In addition to the surveys, we will conduct qualitative interviews with participants, healthcare workers and stakeholders as described below.

#### Acceptability and feasibility of SCOPE-PP – female participants

Surveys with female participants will be used to assess acceptability of PrEP, HIVST and urine TFV testing to increase maternal PrEP use. Acceptability is defined as the perception among women that a given intervention is agreeable, palatable, or satisfactory. Feasibility is defined as the extent to which a new intervention can be successfully used or carried out within a given organization or setting including in relation to patients of differing SES [34].

#### Qualitative methods with women

We will use qualitative methods to capture participants’ lived experiences within their social contexts [35]. Twelve months after enrollment we will sample 30 participants for semi-structured, in-depth interviews. Purposive sampling will be used to help match the characteristics of the study population. Interviews will focus on women’s attitudes about SCOPE-PP interventions including HIVST of self and partner(s), urine testing for recent persistence measurement and option for PrEP delivery for women with poor PrEP continuation and/or persistence (Aim 1).

#### Qualitative methods with male partners

In the intervention arm, we will explore men’s experiences of HIVST, barriers and facilitators and perceptions around maternal PrEP use. Collecting insights from various categories of respondents will allow us deeper understandings of the contexts and challenges involved in SCOPE-PP stepped care implementation, including those in the health system and social landscape. Interviews will cease when saturation of data is reached. Interviews will be digitally recorded, transcribed verbatim and translated.

#### Health provider interviews

Trained interviewers will conduct mixed methods interviews with 20 health care providers (nurses, managers, HIV counselors) who are actively involved in maternal PrEP services in order to assess feasibility of SCOPE-PP including maternal PrEP delivery, counselling, HIVST, PrEP counselling and rapid PrEP delivery, community PrEP delivery and urine TFV testing to improve maternal PrEP use. Data will be collected 12-months after the study enrolment begins in order to assess providers’ real-life experiences with SCOPE-PP vs standard of care (following national PrEP, HIV testing and PMTCT guidelines).

#### Key informant interviews

During study set up, we will interview 10 key informants with experience in managing the clinic (*n* = 5) and making decisions about health policy from the DOH (n = 5) to better understand key facilitators and barriers to maternal PrEP implementation (see Consolidated Framework for Implementation Research [CFIR] constructs in Table 5).

**Table 5 Tab5:** Consolidated Framework for Implementation Research (CFIR) domains and constructs for SCOPE-PP

Domain (description)	Construct (description)	Maternal PrEP specific themes	Participant type
**Intervention characteristics**: Key attributes of interventions influence the success of implementation	**Relative advantage:** Stakeholders’ perception of the advantage of implementing the intervention vs standard of care	Advantage to integration PrEP in ANC services. Advantage of providing self and partner HIVST vs. facility testing, advantage of persistence counseling	Providers, women and partners
	**Complexity**: Perceived difficulty of implementation, reflected by duration, scope, radicalness, disruptiveness, centrality, and intricacy and number of steps required to implement	I am confident that I or my colleague in the clinic can integrate PrEP and HIVST into ante- and postnatal care & I am confident that I or my colleagues can follow up on PrEP in pregnant/postpartum women	Providers
	**Cost**: Costs of intervention and costs associated with implementation including supply, and opportunity costs	Concerns about cost of integration of HIVST (for women & partners) and PrEP into care	Managers and providers
**Outer Setting:** Outer context, factors external to the organization that may influence implementation	**Patient needs and resources:** The extent to which patient needs as well as barriers and facilitators to meet those needs are accurately known and prioritized by the organization	Maternal PrEP & HIVST are compatible with the needs of patients at my clinic and outcomes are achievable irrespective of patient SES	Managers, providers, women and partners
	**External Policies & Incentives:** External strategies to spread interventions including policy and regulations, external mandates, recommendations, and guidelines	Existing guidelines/policies on maternal PrEP and HIVST	Managers and providers
**Inner setting:** Inner context, factors internal to the organization that may influence implementation	**Implementation climate:** The absorptive capacity for change, and the extent to which use of that intervention will be rewarded, supported, and expected within their clinic	Leadership values evidence-based HIV practices such as maternal PrEP and HIVST	Managers and providers
	**Readiness for implementation**: Tangible and immediate indicators of organizational commitment to its decision to implement an intervention	Maternal PrEP and HIVST for patient and provider are essential parts of HIV prevention of my PMTCT program	Managers and providers
**Characteristics of Individuals:** Individuals in the organizations involved in the implementation of the intervention	**Knowledge:** Individuals’ beliefs and value placed on the intervention as well as familiarity with facts, truths, and principles related to the intervention	Awareness of DoH guidelines/policies on maternal PrEP and HIVST & Users’ skilled and provision of PrEP, counseling and HIVST	Managers and providers, women and partners
	**Attitudes:** Individuals’ attitudes toward the intervention	It is more suitable to provide maternal PrEP, HIVST and PrEP to PBFW	Managers and providers

*RCT* randomized control trial, *SCOPE-PP* Stepped care to optimize PrEP in pregnancy and postpartum, *CFIR* Consolidated Framework for Implementation Research, *PrEP* pre-exposure prophylaxis, *HIVST* HIV self-testing, *TFV-DP* tenofovir diphosphate

### Sample size considerations

Based on our PrEP-PP study which observed a mean PrEP continuation and persistence of 30% in postpartum women at 6 months, we expect an improved persistence of > 45% (mean difference of 15%) in the intervention arm of the study. This translates to the mean difference in proportion of women achieving DBS TFV-DP of > 650 fmol/punch in pregnancy and = > 950 in postpartum periods [36] by study arm. This improved PrEP persistence is in line with our pilot study findings of > 60% of women with TFV present in urine after intervention (vs. 17% in control; a 4-fold increase).

We will recruit and enroll 650 pregnant women on PrEP and follow them through 6 months in Step 1. Considering censorship due to pregnancy loss, *n* = 618 will give the study 85% power to detect a 10% + absolute difference in proportions adherent on PrEP (based on DBS of TFV-DP in postpartum period) at a two-sided significance level of 5% (Table 5).

For Step 2, we estimate that after loss to follow-up, censorship and evaluation of the interest of women to continue in the second RCT, we will follow approximately ~ 320 postpartum women who discontinued PrEP in Step 1. This will give us 80% power to detect a difference of 20% in persistence by study arm based on DBS TFV-DP levels.

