#### Study retention

We will ask participants to share their phone numbers as well as the contact of someone clost to them. Study staff will call and SMS participants in both study arms to participate in their study visits. We will conduct home visits if they miss > 1 visit.

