Specifically, in the primary analysis, we will include all women who start PrEP by arm and use product-limit methods including proportional hazards models to estimate the median time to PrEP persistence (at 6 and 12 months) and U-tests and other non-parametric regression models to compare persistence between intervention and control among women using PrEP. In a subsidiary analysis, we will use joint modelling framework^75^ to combine PrEP continuation and persistence measures into a single outcome variable. Women who decide to discontinue PrEP will be included in the analysis as non-adherers.

We will use Consolidated Framework for Implementation Research (CFIR) [37] to analyze qualitative data and structural and participant level acceptability and feasibility of the SCOPE-PP interventions. The CFIR is a conceptual framework that provides systematic assessment of multilevel implementation contexts to identify factors that may influence implementation and effectiveness. The CFIR comprises of five major domains: (1) the characteristics of intervention, (2) inner setting, (3) outer setting, (4) the characteristics of individuals involved, and (5) the process by which implementation is accomplished and 39 constructs that influence the implementation of evidenced-based interventions [38]. We selected 4 CFIR domains and 9 constructs per domain that were most relevant to male partner HIV testing and maternal PrEP in Table 5**.**

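### Step 1: 618 evaluable women give about 74% power for a 10-point difference from the article's own 30% control rate, not 85%, and women without a 6-month blood spot are not provided for

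*Protocol article*

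**What the plan says.** All the planning figures are in the protocol article under Sample size considerations. The control rate is 30%, described as combined continuation and persistence at 6 months postpartum in the team's previous study. The expected intervention rate is above 45%, a 15-point difference. Enrollment is fixed: "We will recruit and enroll 650 pregnant women on PrEP and follow them through 6 months in Step 1". The section then passes to the evaluable number with one reason, "Considering censorship due to pregnancy loss", and claims that "618 will give the study 85% power". In full, the claim is "85% power to detect a 10% + absolute difference in proportions adherent on PrEP", based on postpartum blood-spot drug levels, "at a two-sided significance level of 5" percent. No control rate is attached to that sentence. The table it cites (Table 5) is, in the article, the implementation-framework table.

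The next paragraph, on Step 2, arrives at its number "after loss to follow-up, censorship and evaluation of the interest of women to continue in the second RCT". Step 1 has no corresponding mention of loss to follow-up.

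Under Data analysis, the primary comparison is by intention to treat. Continuation means missing no more than one PrEP pick-up, and the primary analysis covers all women who start PrEP. One scoring rule is given: "Women who decide to discontinue PrEP will be included in the analysis as non-adherers". Under Study retention, the plan is to call and message participants, and "We will conduct home visits if they miss > 1 visit".

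**The concern.** There are two problems with the same sentence. First, a power figure needs a control rate, and the only one the section offers for this outcome (30%) does not reproduce 85% for 10 points. Second, 618 allows for pregnancy loss only, while the outcome depends on a blood sample taken at a study visit about six months later. The article itself describes falling clinic attendance postpartum, and nowhere does it say how a woman with no 6-month sample is classified.

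At stake is how the 10-point claim is read. A reader of a null Step 1 result would think the trial had an 85% chance of detecting a 10-point gain, when on the article's own rate it was nearer three in four, and possibly lower.

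**Working it through.** **Inputs from the article.** Enrolled 650 (325 per arm, 1:1); evaluable 618 (309 per arm); two-sided 5%; control 30%; differences of 10 points (power statement) and 15 points (hypothesis). The pilot's urine-test control rate, 17%, is in the same section.

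**Allowance made.** (650 − 618)/650 = 32/650 = 4.9%, attributed to pregnancy loss.

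**Formula.** Normal approximation for two proportions with n per arm and mean rate p̄ = (p1 + p2)/2:

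- SE0 = √[2 p̄(1 − p̄)/n]
- SE1 = √[(p1(1 − p1) + p2(1 − p2))/n]
- power = Φ[(|p2 − p1| − 1.96 × SE0)/SE1]

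**Attempt to reproduce the 85%.** For 30% vs 40% and n = 309: SE0 = 0.0384, SE1 = 0.0382, z = (0.10 − 1.96 × 0.0384)/0.0382 ≈ 0.65, power 74.2%. Other routes tried:

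| Variant | Power |
|---|---|
| Unpooled variance, 309 per arm | 74.6% |
| All 650 women, 325 per arm | 76.3% |
| One-sided 5% (the article says two-sided) | 83.3% |
| 20% vs 30%, 309 per arm | 82.0% |
| 17% vs 27%, 309 per arm | 85.3% |
| 30% vs 45%, 309 per arm | 97.2% |

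At 30% control, 85% for 10 points would need 407 per arm (814 evaluable). With 618, 85% is reached at a difference of about 11.5 points. The 85% two-sided figure for 10 points is recovered at a control rate of about 17%. (The formula is symmetric, so 73% vs 83% would also serve, but nothing in the article suggests rates that high.)

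**Women without a 6-month blood spot.** The article gives no Step 1 loss rate, so d = 10% and 20% are assumptions, applied after pregnancy loss.

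- *Excluded:* N = 618 × (1 − d) = 556 or 494.
- *Scored as non-persistent, planning rates do not yet count them:* N stays 618 and both rates are multiplied by (1 − d). At d = 10%, 30% vs 40% becomes 27% vs 36%. At d = 20%, it becomes 24% vs 32%.
- *Scored as non-persistent, planning rates already count them:* N and the rates are unchanged.

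| Handling | 30% vs 40%: d = 10% / 20% | 30% vs 45%: d = 10% / 20% |
|---|---|---|
| Excluded | 69.7% / 64.5% | 95.7% / 93.4% |
| Failures, not yet in the rates | 67.4% / 60.1% | 94.6% / 90.4% |
| Failures, already in the rates | 74.2% / 74.2% | 97.2% / 97.2% |

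If 17% vs 27% was the intended basis, exclusion at 10–20% loss takes 85.3% to 81.4–76.7%, so the handling question remains under that rate too.

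**The case against.** A reader might infer that loss to follow-up must push the evaluable number below 618, and that this is why 85% is not delivered. The documents do not support that. Intention to treat, an analysis of all women who start PrEP, and a definition under which missing more than one pick-up is failure all suggest that most women who stop attending stay in the denominator as failures, with no blood result needed. Product-limit methods censor lost women; they do not drop them. The 30% is itself a composite that may already count such women. The Step 2 deduction may simply describe how many Step 1 women reach the second randomization. Most of the gap, 85% to 74%, is there before any woman is lost.

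All of that stands, and it limits the loss point to what is unstated. It does not settle the matter. The only explicit scoring rule covers women who decide to stop, not women who cannot be traced or who miss only the 6-month sample, and the article does not say whether the 30% includes them.

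It can also be said that the claim is for 10 points *or more*, and that 85% is reached at about 11.5. But the sentence names 10 as the lower limit, and there the power is 74%. Finally, confidence intervals will be reported, so a null result need not be judged by planned power, and attrition detail may sit in a fuller document. That lowers the stakes, but the 85% is printed here and does not follow from the rate printed beside it.

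**Conclusion.** The point holds in two parts. The firm part needs no assumption about loss: with the article's 30% control rate, 618 women give about 74% power for 10 points, roughly 11 points below the stated 85%, and even 650 give 76%. The mismatch lies between the power figure and its control rate, not in the subtraction from 650 to 618.

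The second part is conditional. Because women without a 6-month blood spot are not classified, power for 10 points could fall to about 70–65% (excluded) or 67–60% (failures not yet counted in the rates), or not fall further at all (already counted). These ranges rest on assumed losses of 10–20%.

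Neither part threatens the hypothesized 15-point effect, for which power is 97% at 618 and about 90% or more in every case shown. It would be wrong to read this as an underpowered trial; what needs correcting is the 10-point statement.

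**What to change.** Enrollment stays as it is. Under Sample size considerations:

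1. State the control rate behind the Step 1 power and restate the figures: at 618, about 74% for 30% vs 40% and about 97% for 30% vs 45%. If 17% vs 27% was meant, say so and justify that rate for the blood-spot outcome.
2. State, there and under Data analysis, that women without a 6-month blood spot are scored as non-persistent, in line with the intention-to-treat and missed-pick-up rules, and whether the 30% and 45% already count them.
3. If they are to be excluded instead, give the loss allowance and the power at the reduced number: about 65–70% for 10 points and 93–96% for 15 points at an assumed 10–20% loss.

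The cost is a few sentences and a less favorable figure for 10 points. The case for the hypothesized effect is unaffected.

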### Data management

Trained study staff will capture data electronically via a secure data software, RedCap, that will include range checks and rules to promote dat quality. The trained data manager will monitor entry for completeness and consistency. They will provide the team with weekly and monthly reports to correct any missing, incomplete or inconsistent data.

Specifically, in the primary analysis, we will include all women who start PrEP by arm and use product-limit methods including proportional hazards models to estimate the median time to PrEP persistence (at 6 and 12 months) and U-tests and other non-parametric regression models to compare persistence between intervention and control among women using PrEP. In a subsidiary analysis, we will use joint modelling framework^75^ to combine PrEP continuation and persistence measures into a single outcome variable. Women who decide to discontinue PrEP will be included in the analysis as non-adherers.

We will use Consolidated Framework for Implementation Research (CFIR) [37] to analyze qualitative data and structural and participant level acceptability and feasibility of the SCOPE-PP interventions. The CFIR is a conceptual framework that provides systematic assessment of multilevel implementation contexts to identify factors that may influence implementation and effectiveness. The CFIR comprises of five major domains: (1) the characteristics of intervention, (2) inner setting, (3) outer setting, (4) the characteristics of individuals involved, and (5) the process by which implementation is accomplished and 39 constructs that influence the implementation of evidenced-based interventions [38]. We selected 4 CFIR domains and 9 constructs per domain that were most relevant to male partner HIV testing and maternal PrEP in Table 5**.**

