## Methods

### Aims

The aims of the study are to:*Aim 1*: Evaluate the impact of SCOPE-PP interventions on PrEP persistence in pregnancy and early postpartum (peripartum) (Step 1) and postpartum women (Step 2)Step 1 (randomize 650 pregnant women actively taking PrEP at the time of enrollment):Intervention: Enhanced adherence counseling through biofeedback and rapid PrEP collection following HIVSTPrimary Outcome 1: PrEP continuation and persistence per urine tenofovir (TFV) at 6-months after randomization (verified post hoc via dried blood spots [DBS] analysis of tenofovir diphosphate [TFV-DP]).Hypothesis 1: Enhanced adherence counseling and rapid PrEP collection will improve PrEP continuation and persistence by > 15%.Step 2: We will randomize ~ 325 postpartum women from Step 1 who disengaged from PrEP during the first 6-months post enrollment and desire to stay on PrEP to:Intervention 1: Rapid PrEP collection following HIVST and differentiated model of community-based PrEP delivery.Intervention 2: Enhanced adherence counseling through biofeedback in the clinic and rapid PrEP collection following HIVSTPrimary Outcome 1: PrEP continuation and persistence per urine TFV at 6-months after randomization in Step 2 (verified post hoc via DBS analysis of TFV-DP).Hypothesis 2: Among postpartum women who struggle to engage with PrEP within the first 6-months postpartum, differentiated PrEP delivery (in community pick up points) will improve PrEP continuation and persistence by > 15% compared to standard-of-care (intensive counseling and facility PrEP delivery) at 12-months postpartum.*Aim 2****:*** Evaluate the cost effectiveness and equity impact of SCOPE-PP vs. standard of care. Within a trial-based cost-effectiveness analysis, we will estimate provider costs and primary outcomes of SCOPE-PP in terms of PrEP continuation and persistence per urine tenofovir at 6-months and 6-months after randomization in Step 2. Thereafter, in a model-based economic evaluation that integrates HIV-infections averted, we will estimate HIV-treatment cost offsets in order to estimate lifetime costs and DALYs averted. The resulting incremental cost per DALY averted will be compared to a South African cost-effectiveness threshold to assess value for money [28].

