**Randomization of pregnant women on PrEP (= > 25 weeks gestation)**			
**Baseline Study visit**	In clinic: PrEP offer, standard counseling	In clinic: PrEP offer, standard counseling	In study site (behind clinic): • Consent form • Survey • Reimbursement for time
**1 month clinic visit**	In clinic: PrEP refill and standard counseling, urine testing (no feedback)	In clinic: PrEP refill with urine testing and feedback on PrEP levels in urine	Standard monitoring No reimbursement for time
**3 month Study visit**	In clinic: PrEP refill and standard counseling, urine testing (no feedback) With standard HIV testing/HIVST	In clinic: PrEP refill with urine testing and feedback on PrEP levels in urine With standard HIV testing/HIVST	In study site: • Blood collection • Survey • Reimbursement for time
**6 month** **Study visit**	In clinic: PrEP refill and standard counseling, urine testing (no feedback) With standard HIV testing/HIVST	In clinic: PrEP refill with urine testing and feedback on PrEP levels in urine With standard HIV testing/HIVST	In study site: • Blood collection • Survey • Reimbursement for time
**If participant continues on PrEP and adherent based on urine testing, can continue in study according to following visits. If not adherent or discontinues, can participate in RCT Step 2 (LATE-PREP-P).**			
**9 month clinic visit**	In clinic: PrEP refill and standard counseling, urine testing (no feedback) With standard HIV testing/HIVST	In clinic: PrEP refill with urine testing and feedback on PrEP levels in urine With standard HIV testing/HIVST	Standard monitoring No reimbursement for time
**12 month Clinic visit**	In clinic: PrEP refill and standard counseling, urine testing (no feedback) With standard HIV testing/HIVST	In clinic: PrEP refill with urine testing and feedback on PrEP levels in urine With standard HIV testing/HIVST	Standard monitoring No reimbursement for time
**15 month Study visit**	In clinic: PrEP refill and standard counseling, urine testing (no feedback) With standard HIV testing/HIVST	In clinic: PrEP refill with urine testing and feedback on PrEP levels in urine With standard HIV testing/HIVST	In study site: • Blood collection • Survey • Reimbursement for time

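### The primary analysis estimates a median time to persistence with no defined event; the median can be equal in both arms despite a real effect, and it is not the 6-month proportion on which the trial is powered

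*Protocol article*

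**What the plan says.** The last part of the Data analysis section specifies the primary analysis: take those who begin PrEP in each arm, then "use product-limit methods including proportional hazards models to estimate the median time to PrEP persistence (at 6 and 12 months". It gives no event, time origin or censoring rule, and adds that women who stop PrEP count as non-adherers.

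The rest of the article treats the outcome as yes or no at one time:

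- **Aims** states each hypothesis as an improvement of more than 15% in continuation and persistence.
- **Sample size considerations** cites an earlier study that "observed a mean PrEP continuation and persistence of 30% in postpartum women at 6 months" and continues: "we expect an improved persistence of > 45% (mean difference of 15%) in the intervention arm of the study". Power is then given for proportions: "618 will give the study 85% power to detect a 10% + absolute difference in proportions adherent on PrEP".
- **Data analysis**, in its step-wise paragraph, names a proportion at 6 months: no more than one missed pick-up, and TFV-DP at or above the stated cut-off.

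On entry state, Aims says Step 1 will "randomize 650 pregnant women actively taking PrEP at the time of enrollment", and the Step 1 recruitment section also admits women starting PrEP at baseline. Step 2 takes women who discontinued or had a negative urine result.

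On sampling, Table 1 lists "In study site: • Blood collection • Survey • Reimbursement for time" at months 3, 6 and 15, and urine testing at months 1, 3, 6, 9, 12 and 15. Table 2 lists blood only at the 9-month visit, and its community-delivery cells list no urine test.

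**The concern.** A product-limit median needs an event that happens once and can be dated. Persistence can be present, absent and present again.

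- If the event is reaching persistence, Step 1 women already on PrEP may have had it before time zero. Table 1 lists no baseline blood with which to identify them.
- If the event is loss of persistence, it has already happened for Step 2 women before they enter.

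Either choice therefore fails in one of the steps, and the sentence covers both.

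The headline estimate could then read as no difference when the intervention works, because both medians fall on the same visit. A median or a hazard ratio also does not give the 15-point difference that the hypotheses name, and no power is stated for either. An analyst following the sentence literally would report something other than the result the trial was sized to deliver.

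**Working it through.** **The plan's own figure.** No sample size is given for a median or hazard ratio. The only Step 1 figure is 85% power for a 10-point difference with 618 women (309 per arm at 1:1), two-sided 5%. With p̄ the mean of the two rates:

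power = Φ{[(p2 − p1) − 1.96 √(2 p̄(1 − p̄)/n)] / √([p1(1 − p1) + p2(1 − p2)]/n)}

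- 30% vs 40%: (0.100 − 0.0752)/0.0382 = 0.65, power 74.2%. The stated 85% is not reproduced from the 30% control rate.
- 30% vs 45%: (0.150 − 0.0763)/0.0385 = 1.91, power 97.2%.

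The mismatch with 85% is a separate matter. What counts here is that the power basis is a difference in proportions.

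**Event = reaching persistence.** The 30% and 45% are proportions at month 6, not shares ever persistent by then.

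- Read as cumulative, F(6) = 0.30 and 0.45. Neither median is reached by month 6. With constant hazard, median = 6 ln 2 / [−ln(1 − F(6))] = 11.7 and 7.0 months, and F(12) = 1 − 0.70² = 0.51 and 1 − 0.55² = 0.70.
- Read as status at each visit, with the same rates and independent results at months 3 and 6 (an assumption), the share ever persistent by month 6 is also 0.51 and 0.70. Both medians are then reached at month 6.

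**Event = loss of persistence.** S(6) = 0.30 and 0.45, so 70% and 55% have had the event and both medians are reached by month 6. With constant hazard:

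- True median = 6 ln 2 / (−ln S(6)) = 4.159/1.204 = 3.5 months (control) and 4.159/0.799 = 5.2 months (intervention).
- S(3) = √0.30 = 0.548 and √0.45 = 0.671. Both curves are above 0.50 at month 3 and below it at month 6, so events dated at months 3 and 6 give a median of 6 months in both arms.
- In 20,000 simulations with 309 women per arm, the estimated median was 6 months in 95.3% of control and 96.2% of intervention runs. Both arms would show 6 months in about 0.953 × 0.962 = 92% of trials. Adding a month 1 observation left this unchanged (95.4% and 96.1%).

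**Sensitivity to hazard shape (Weibull, same 6-month rates).**

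| Shape | True medians, months (control, intervention) | S(3) (control, intervention) | Medians on month 3 and 6 grid |
|---|---|---|---|
| 0.5 | 2.0, 4.5 | 0.427, 0.569 | 3 and 6 |
| 1 | 3.5, 5.2 | 0.548, 0.671 | 6 and 6 |
| 2 | 4.6, 5.6 | 0.740, 0.819 | 6 and 6 |

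The same 15-point effect thus appears as a gap of 0 or 3 months, according to whether one arm's curve has crossed 50% by month 3.

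**Step 2.** Table 2 lists one blood collection, at month 9, so an event dated by blood has one possible time. The primary time point is 6 months after the second randomization, a visit at which Table 2 lists no blood.

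**The case against.** The strongest reply is that the step-wise paragraph of the same section already plans the 6-month proportion, with intention-to-treat and 95% confidence intervals stated for the comparisons, so the right analysis is present. Ties, interval censoring and time origin are also details that a separate analysis plan may settle. Both points are fair. Neither removes the conflict, because the later sentence says specifically what the primary analysis is and names a different quantity. A later plan would have to overrule it.

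Two stronger readings are tempting, and the article does not support them.

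- **That the median is unreached in both arms.** This needs the event to be reaching persistence and the 6-month proportions to be cumulative. The article says neither, gives the intervention rate as a floor and looks out to 12 months. Under loss of persistence both medians are reached by month 6.
- **That each Step 1 median must be 3 or 6 months.** This holds only for events dated by blood in the first 6 months. Urine is also tested at month 1, urine is the measure named for the primary outcome in Aims and Outcomes, and missed pick-ups supply further dates. Timing is still tied to scheduled contacts.

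It is also fair that reaching persistence is a coherent event within Step 2. The difficulty is that one undefined phrase serves both steps.

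**Conclusion.** The concern stands: the named primary analysis has no workable event for both steps, its median is too coarse to be relied on to show a real difference, and it does not estimate the difference in 6-month proportions that the hypotheses, outcome definition and power use. These points rest on the text and the visit tables alone.

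The size of the coarseness depends on assumptions: loss of persistence as the event, 30% vs exactly 45% at month 6, constant hazard, and events dated at visits. Under these, true medians of 3.5 and 5.2 months would usually both be reported as 6. With hazard concentrated early, the estimate would instead show 3 against 6 months.

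A reader might take the 97% power as showing that the sample size suits the proportion in general. It applies to 30% vs 45% only. For the 10-point difference stated in Sample size considerations, with 30% in controls, power is about 74%.

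**What to change.** In the Data analysis section, replace the primary-analysis sentence. For each step, the primary analysis becomes the between-arm difference in the proportion meeting the continuation-and-persistence definition 6 months after that step's randomization, with its 95% CI, in all women randomized to that step, with discontinuers counted as non-persistent. A chi-square test or binomial regression would serve.

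Reconcile the Step 2 time point with the blood-sampling visit in Table 2.

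If a time-to-event analysis is kept, make it secondary. Define the event as first missed refill or first sample below the cut-off, date it from randomization, fit a discrete-time or interval-censored model, and report no median. Because the continuation definition tolerates one missed pick-up, say that this event is stricter than the binary outcome.

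For Step 1 the cost is wording only: the month 6 blood and urine are already scheduled. For Step 2 it is wording too, unless the reconciliation changes the sampling schedule.
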